### Site-wise and combined analysis plan

While site-wise analyses will provide insights into differences across study sites, results will also be presented for all sites combined and separately for the Asia and Africa regions. Variations in care pathways will be addressed through hospital-level stratification of staff, medicine, and consumable costs, using infant-days as weights to derive site averages. Costs for partial treatment will be estimated at the hospital level by using infant-days as weights for infants receiving partial treatment. Overall costs for enrolled infants will be estimated at the site level using the weighted average of those receiving recommended treatment and those receiving partial treatment. The combined average across all sites will be estimated by using enrolled infants at each site as weights for each treatment arm. The number of infants receiving at least 80% of the recommended treatment in each treatment arm will be used as weights to estimate the combined average hospital costs for the recommended treatment across all sites.

Average weighted inpatient bed costs at the site level will be estimated across all hospitals for each treatment arm using the number of SYIs enrolled in paediatric and newborn wards as weights. Combined inpatient bed costs will then be estimated using the total number of SYIs enrolled in these wards as weights at each site. Average operational costs will also be stratified at the hospital level within each site by using the number of SYIs assessed as weights, and site-stratified for combined analyses using the number of SYIs enrolled as weights at each site.

Average household costs – including registration, food, transport, and wage loss per SYI – will be calculated at the site level using the household survey sample size as the denominator. For pooled analyses, enrolled SYIs will be used as weights across sites. Both the median and the arithmetic mean will be reported to describe the distribution of costs for each variable. Uncertainty in CE will be presented using site-level, regional-level, and pooled ICERs plotted on CE planes. In addition, the mean INB will be estimated and pooled across sites, and 95% confidence intervals will be derived using the *t*-distribution based on site-level variation. An INB greater than zero will indicate that the intervention is cost-effective at the specified willingness-to-pay threshold.

All costs will be presented in 2024 USD. CE results will be interpreted in relation to country-specific willingness-to-pay thresholds and opportunity cost considerations. These findings will provide context-specific evidence to inform national policy decisions rather than relying on outdated GDP-based benchmarks [31].

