### Costs framework

The cost will be assessed from both the hospital and household perspectives. From the hospital perspective, medical treatment costs will be determined at each study hospital across all sites in both the intervention and control arms (**Table 1**, **Table 2**). Additionally, the household's costs will be separated into medical and non-medical costs. The hospital's indirect operational costs and households' opportunity costs in terms of wage loss will also be estimated. The costs will be weighted by infant days for each hospital, separately for the control and intervention arms, to obtain site-specific average costs for each item. To generate combined estimates, we will pool site-specific average costs across all sites to produce a single multi-country mean cost for inpatient and outpatient management, respectively.

**Table 1 T1:** Framework for provider costs under RCT1: outpatient versus inpatient management of young infants (0–59 days) with low-mortality-risk PSBI signs

Cost category	Intervention arm: outpatient treatment	Control arm: inpatient treatment
Place of treatment	Outpatient/ambulatory care	Hospital inpatient care
Antibiotic regimen	Injectable gentamicin once daily for 2 days plus oral amoxicillin twice daily for 7 days	Injectable ampicillin (2–4 times daily depending on age) plus injectable gentamicin once daily for 7 days
Staff costs	Outpatient assessment, counselling, injections preparation (canula), gentamicin administration, follow-up visits	Inpatient assessment, nursing care, injections preparation (canula) + administration, monitoring and supportive care
Medicine costs	Gentamicin and oral amoxicillin	Ampicillin and gentamicin
Consumables	Syringes, needles, cotton swabs, gloves, cannula, spirit	Syringes, needles, intravenous supplies, cotton swabs, gloves, cannula, spirit
Inpatient bed costs	Not applicable	Included for the duration of hospitalisation. Captures costs in the paediatric wards, such as costs of non- consumables, utilities, security, and laundry
Operational and indirect costs	Training, supervision, communication, administration and programme support	Training, supervision, communication, administration and programme support
Weighting approach for pooled analysis	Infant-days (number of infants treated and days each medicine or consumable is used)	Infant-days (number of infants treated and days each medicine or consumable is used)

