Coverage of sick YIs (SYI) assessed, enrolled and treated under both RCT1 and RCT2 for control and intervention.Data on two outcome variables for all SYI covered under different treatment arms. Well-trained independent outcome assessor visits all enrolled cases on days two (only for RCT1), four, eight, and 15 after the initiation of treatment to assess the study outcomes in both intervention and control arms.Average annual salaries of nurses, paediatricians, medical officers and any other staff supporting treatment. To calculate staff costs per minute, data will be collected on the average number of days in a month and the average number of hours in a day that staff work.Staff time will be considered only for activities that are linked to hospital staff and not those linked to research staff, such as outcome assessment or treatment documentation (**Table 1**, **Table 2**). The activities for the staff time will be based on a pre-defined implementation strategy [21,22].Data will be collected for SYI that receive at least 80% of the treatment (recommended treatment) and those who receive <80% of seven-day (<5.5 days) treatment (partial treatment). The latter occurs due to a treatment failure, a change in treatment, readmission, left voluntarily, or death. For the recommended treatment, we will collect costs for the seven-day treatment period following the initial assessment, across both study arms and both trials. For partial treatment, medical costs will be calculated for an average treatment period of three days in RCT1 after the initial assessment, and for two days in RCT2 in both inpatient and outpatient arms after randomisation. Costs for enrolled SYI will be weighted by the proportion of participants receiving 80% recommended treatment and those receiving partial treatment, with weights set to SYI for each group. This prevents any child randomised and enrolled from being missed. Costs due to complications, changes in treatment, and/or readmission are outside the seven-day recommended treatment window in both study arms of both trials and will not be collected.Data on staff time per visit for an activity and the number of visits undertaken for each activity during the recommended treatment period will be collected by interviewing at least 3–5 staff of each type at each hospital.The staff time for all visits during the treatment period will be weighted by the number of days an infant receives the activity and the number of YI receiving the activity (defined as weighted by infant days). For the first activity assessment on presentation at the hospital, the number of SYI will be all enrolled for a given treatment, whether partial or recommended. For all other activities, SYI who receive 80% recommended treatment will be considered to have received seven days of treatment, and those receiving partial treatment for an average of three days to calculate the costs for those enrolled.The average exchange rate used to convert all the cost estimates in local currency into USD will be for 2024, the period for which the salaries of providers, prices and household costs will be reported. It will ensure consistency, and inflation rate adjustments will not be needed for cost calculations. The recommended treatment period will be seven days for inpatient treatment in the control arm and seven days for outpatient treatment in the intervention arm for RCT1. For RCT2, the average length of inpatient treatment is 48–72 hours, prior to a negative CRP laboratory test. In RCT2, the control group after randomisation will continue receiving inpatient care for five days, while the intervention group will be discharged from the hospital on oral amoxicillin for five days to be taken at home. Both arms will share the initial hospitalisation costs during the first two days in RCT2, including CRP test costs (including staff time, kits, and laboratory costs).The data on quantities used of injection gentamicin, injection ampicillin and oral amoxicillin will be as per the recommended treatment and partial treatment per SYI for each treatment arm under each RCT.The number of SYI receiving specific medicines and consumables for each arm under both RCTs will be calculated based on the numbers receiving recommended treatment and those receiving partial treatment.Information on types and quantities of consumables required with each medicine will be collected separately for each hospital and each arm under both RCTs. The cost of medicines and consumables will be charged per size in which they are dispensed. Medicine dosage varies with the weight of the YI [21,22]. Price will be taken for full strength, and the rest will be marked as wastage. Price data will be taken from the hospital's pharmaceutical department (if available); otherwise, the market price or the WHO price will be used.Data on annual financial expenditures and admissions in the newborn intensive care units or paediatric wards where YI with PSBI are treated as inpatients at the hospital will be collected and allocated based on patient days to calculate the inpatient bed costs/ SYI treated as an inpatient. These expenditures include administration, utilities, laundry, security, data management, internet, non-consumables and other costs in the hospital inpatient ward.Hospital ambulance to transport enrolled SYI under a specific treatment arm is a cost to the hospital. It is difficult to get this information separately for each enrolled SYI under different treatment arms from the hospital data. Indirect estimation based on the average trip cost and the number of SYI using free public ambulances, estimated from household data for each treatment arm in RCT1 and RCT2, will be used.Hospital data will also be collected for operational costs, which help to strengthen the assessment, identification, and treatment of SYI with PSBI. These include training, supplies, and communication. The total costs under these three will be estimated per SYI assessed. Staff training costs include the costs of development of training material and training cost per staff per day based on the per diems, honorarium for trainers, venue and refreshment costs. Total training costs will be calculated for all staff who were used to assess and treat SYI and will be estimated per SYI assessed. Training costs for research staff for outcome assessment or data collection will not be collected or included. Price and quantities of supplies used during the assessment, such as timers, thermometers and weighing scales, will be prorated for PSBI assessed. Communication costs, include job aids or educational material, and the cost of videos developed and played at the hospitals for educating the mothers about the danger signs. Data will be collected on item quantities and prices from hospitals to assess total costs and costs per SYI assessed.

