### CEA

CE will be evaluated by estimating the ICER, defined as the difference in mean costs between the intervention and control arms divided by the difference in effectiveness between the two arms: ICER = (C_1_ − C_2_) / (E_1_ − E_2_), where C_1_ are the average costs for the intervention group; C_2_ are the average costs for the control group; E_1_ is the mean effectiveness measure for the intervention group, and E_2_ is the mean effectiveness measure for the control group. We will use societal costs – hospitals and households’ – medical costs (staff time, medicines, consumables); hospital inpatient bed cost, operational costs and households’ non-medical costs (transport, food and wage loss) for ICER calculations for all randomised SYI in both arms. We will also report ICER from only the provider/payer perspective using only medical costs for all enrolled SYI and those receiving at least 80% of the recommended seven-day treatment as a sensitivity analysis [27].

For RCT2, while the baseline costs will be presented for both pre- and post-randomisation for both study arms, the costs for ICER calculations will be compared only post-randomisation.

For each RCT, cost measures will be evaluated in both the control and intervention arms for all enrolled infants who receive either the full seven-day treatment or partial treatment. Effectiveness will be assessed in the same population based on clinical outcomes recorded on days two (for RCT1), four, eight, and 15 following treatment initiation. The ICER will be calculated for each RCT to assess whether the intervention is more cost-effective than the control.

There can be 4 case scenarios for ICER (**Figure 2**):

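### The at-least-80% sensitivity analysis pools hospital costs over sites with each arm's own post-randomisation count, so site mix can enter its cost difference

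*Protocol article*

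**What the plan says.** Two cross-site weighting rules stand next to each other in the Protocol article, section Site-wise and combined analysis plan.

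- All enrolled infants: "The combined average across all sites will be estimated by using enrolled infants at each site as weights for each treatment arm". Within each site, full and partial courses are first recombined: "Overall costs for enrolled infants will be estimated at the site level using the weighted average of those receiving recommended treatment and those receiving partial" courses.
- Recommended-treatment hospital cost: "The number of infants receiving at least 80% of the recommended treatment in each treatment arm will be used as weights".

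The section CEA says where each population is used. The main societal costs serve "for ICER calculations for all randomised SYI in both arms". The provider/payer ICER is reported for all enrolled infants and for "those receiving at least 80% of the recommended seven-day treatment as a sensitivity analysis".

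The section Hospital data lists what puts an infant in the partial group: "The latter occurs due to a treatment failure, a change in treatment, readmission, left voluntarily, or death". All of these happen after randomisation.

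Other components are less definite. For bed costs, "Combined inpatient bed costs will then be estimated using the total number of SYIs enrolled in these wards as weights at each site". Pooled operational and household costs use enrolled infants as weights. None of these three rules says whether the cross-site count is taken per arm.

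For the incremental net benefit (INB), the section CEA forms the cost and effect differences within each site. They are pooled afterwards, with weights that are not stated.

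**The concern.** When each arm is averaged over sites with its own weights and the averages are subtracted, the result is the average within-site difference plus a term for the difference in site mix. Prices and salaries can be expected to differ between sites in six countries, so this term need not be small.

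Randomisation protects weights based on enrolled infants. It does not protect weights based on completers. The article's introduction and discussion name cost, distance, wage loss and cultural constraints as barriers to hospital care. Completion could therefore plausibly differ between inpatient and outpatient care, and by a different amount at each site.

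The weights matter more here than in a usual completer analysis. Under Hospital data and Estimation of medicines and consumables costs, a completer is costed as a standard seven-day course from hospital-level times, quantities and prices. Within a site, cost per completer thus depends largely on the regimen and local prices, and little on who completes. Cross-site weighting is then a main route by which differential completion can move the cost difference.

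At stake is the reading of the sensitivity analysis. It could appear to confirm or contradict the main result because of site mix alone. The pooled ICER and the pooled INB could also rest on different incremental costs for the same trial.

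**Working it through.** The article gives no site-by-arm counts, completion rates, site costs, allocation ratio or stratification. There is no stated figure to reproduce. All numbers below are assumptions that show the mechanism and its range.

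**Formula.** Let C1s and C0s be the mean costs at site s in the intervention and control arms, p1s and p0s each arm's share of its weight at site s, and ws a common share.

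- Planned: D_arm = Σ p1s·C1s − Σ p0s·C0s
- Common weights: D_common = Σ ws·(C1s − C0s)
- Site-mix term: D_arm − D_common = Σ (p1s − ws)·C1s − Σ (p0s − ws)·C0s

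**Two sites.** Control costs USD 40 and 200, intervention costs USD 15 and 60, 100 enrolled per arm and site. Completion is 90% and 70% in control, and 90% at both sites in intervention.

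- Control, completer weights: (90×40 + 70×200)/160 = 110
- Intervention, completer weights: (90×15 + 90×60)/180 = 37.5
- Planned difference: 37.5 − 110 = −72.5
- Common weights: 37.5 − (40 + 200)/2 = 37.5 − 120 = −82.5
- Gap: 10/82.5 = 12%, with no within-site cost changed

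**Seven equal sites.** Control costs USD 20, 30, 40, 55, 70, 90 and 120 (mean 425/7 = 60.71). Intervention costs are USD 20 lower at every site (mean 40.71). Enrolment is balanced, and intervention completion is 95% everywhere. With any common weights the answer is −20.00.

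| Control completion | Weighted control mean | Planned difference | Site-mix term |
|---|---|---|---|
| 80% at every site | 60.71 | −20.00 | 0.00 |
| 95% falling to 85% as cost rises | 59.52 | −18.81 | +1.19 |
| 95% falling to 65% as cost rises | 56.70 | −15.98 | +4.02 |
| 65% rising to 95% as cost rises | 64.73 | −24.02 | −4.02 |
| 50% at the two dearest sites, 95% elsewhere | 53.78 | −13.07 | +6.93 |

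Example, third row: completion steps of 0.05 from 0.95 to 0.65 sum to 5.6. The weighted sum is 19 + 27 + 34 + 44 + 52.5 + 63 + 78 = 317.5, and 317.5/5.6 = 56.70.

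The first row matters as much as the last. A large overall gap in completion (95% against 80%) does no harm if it is the same at every site.

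**Enrolled weights.** With the same seven sites:

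- Arms balanced by site: −20.00, no distortion.
- Unstratified 1:1 randomisation, 20,000 simulated draws: mean distortion about 0, with SD about USD 0.7, 0.9 and 1.8 for 1400, 700 and 200 infants per site.

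In the two-site example, a single opposite imbalance of 48/52 in control and 52/48 in intervention gives (0.52×15 + 0.48×60) − (0.48×40 + 0.52×200) = 36.6 − 123.2 = −86.6. That is 4.1/82.5 = 5% away from −82.5. It is one possible chance draw and not a systematic shift.

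**The case against.** A reader might infer that the main ICER is biased because its weights are also taken by arm. The documents do not support that. Weighting site means by the infants enrolled in an arm gives the ordinary intention-to-treat mean for that arm. Enrolled counts come from randomisation, so site mix adds only noise centred on zero. If randomisation was balanced by site, which this article does not say, even that nearly vanishes.

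A reader might also infer that any difference in completion between arms biases the sensitivity result. That is not so, as the uniform 80% case shows. Nor can it be said that every pooled component uses arm-specific weights, because the text does not settle this for bed, operational and household costs.

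It can fairly be said that the completer weights reach only a sensitivity analysis. They give the plain completer mean in each arm, and they fit the section Outcomes, where the effectiveness denominator differs between enrolled and recommended-treatment infants. The within-site INB already avoids the cross-site problem. The illustrations are constructed, and in none of them does the cost difference change sign.

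All of this stands and limits the point. It does not justify the completer weights. A mean that matches its own denominator can still compare arms with different site mixes, and the INB does not correct the sensitivity ICER.

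**Conclusion.** The point holds for the provider/payer sensitivity analysis in infants who received at least 80% of treatment. Its pooled cost difference and ICER can carry a systematic site-mix term, in either direction, when completion varies across sites differently by arm and tracks site cost. In the illustrations the term is USD 1.2 to 6.9 on a true saving of USD 20. Those sizes rest wholly on assumed costs and completion rates, and the actual size cannot be found from the documents.

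For the all-randomised ICER this is a minor matter of precision and consistency. The site-level INB is unaffected by cross-site weights.

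Two limits remain. Common site weights do not remove the selection of completers within a site. Hospital averages within a site also use arm-specific infant-days (Costs framework: "The costs will be weighted by infant days for each hospital, separately for the control and intervention arms"). That is a further weight formed after randomisation, and it is not sized here.

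**What to change.** State one set of site weights, total randomised per site over both arms, and use it for both arms. Equivalently, compute the cost and effect differences within each site, as the plan already does for the INB, and pool both with those weights.

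Apply this above all to the at-least-80% provider/payer analysis, with the same weights for costs and effectiveness and for every cost component in the total. For consistency, use it also for the pooled and the Asia and Africa ICERs.

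The cost is a change of weights in the spreadsheet. The inputs are already collected, and site-level results do not change. The report should add that the at-least-80% comparison still carries selection of completers within sites.

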
#### Household cost data

Household expense data will be collected during the last nine months of the study at each site to capture the out-of-pocket expenditures that households incur during the treatment of enrolled SYI under both treatment arms for RCT1 and RCT2. Data will be collected from at least 10% of SYIs enrolled under each arm at each site. These sampled households will be assumed to be representative of all treated YIs both temporally and geographically. Further, the household data for the seven-day treatment period will be collected either on day eight or 15 of the outcome visit or at most within two weeks from the last outcome assessment, to avoid recall bias. Where available, caregiver-reported expenditures will be cross-checked with receipts or facility payment records to enhance accuracy.Standardised household questionnaires will be used across all sites to collect data on medical and non-medical costs using the REDCap tool [25,26]. Training will be provided to collect data using these forms, and pilots will help improve the tool and data quality. Data inconsistencies will be identified, discussed with the sites and corrected at the analysis stage.Data will be collected on the type of treatment arm and duration of treatment. Direct treatment costs for each component will be collected in local currency from sampled households in each treatment arm for RCT1 and RCT2 at each site. Total medical expenses by households will be collected for registration and consultation fees, expenditures on medicines such as amoxicillin, ampicillin, gentamicin and other supportive care such as paracetamol, consumable supplies such as syringes, needles, canulas, bandages, spirits, gloves, laboratory expenses such as x-ray, blood work, urine tests (investigation costs), or any other payments to hospitals. Non-medical expenses, such as transport and food, will be recorded for seven days. Data will include the mode of transportation and expenses incurred by any household member on round-trip trips during the treatment period. Similar information will be collected on food, with the amount spent outside the home during the days the infant had to stay at or visit the hospital.Indirect expenses are opportunity costs, or the costs incurred by the household in terms of wage loss to take care of the sick child. Data will be collected from parents and caretakers who lost their wages due to time spent caring for the child. Household work that does not entail income will not be included in the opportunity cost. Data will be collected on the type of occupation/source of income, average earnings on a daily, monthly, or yearly basis (in the provided ranges), and the number of days not able to work to take care of the SYI. Maximum seven days of wage loss will be considered.

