
### Statistical analysis procedures

The statistical analysis for the hospital cost data will be done in Microsoft Excel (Microsoft, Redmond, WA, USA). The data from all facilities where infants are randomised will be entered into a structured Excel document. The average costs per SYI for staff, medicines, consumables, and inpatient bed costs, will be calculated as outlined below. Mean, median, and 95% confidence intervals will be calculated using t-values per SYI receiving recommended or partial treatment for each of the cost variables at the hospital, as well as at the household level. The medical treatment costs per SYI will be the sum of the weighted average of staff costs, medicines, consumables, inpatient bed costs, and operational costs, where weights are infant-days for those receiving recommended and partial treatment. Non-medical costs on transport, food and wage loss per SYI will be added to total medical costs per SYI to estimate the total societal costs for the control and intervention arms for RCT1 and RCT2 separately. Household payments for both medical and non-medical treatment would be added to calculate the household burden in total societal costs.

The treatment outcomes for all enrolled in the control and intervention arms will be used to estimate incremental CE ratios (ICERs) for both RCTs.

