### Estimation of the household costs

Direct treatment costs reported by the households for each of the individual components will be compared, and data quality checks will be performed. Expenses incurred by households for each component will be estimated per SYI, based on the number of households in the sample after removing outliers. Outliers will be flagged using the median-absolute deviation and values exceeding plausible ranges (*e.g.* food costs exceeding World Bank *food per capita* benchmarks and wage losses based on World Bank *per capita* benchmarks).Household expenses included for CEA will be for registration/ consultation, recommended medications (gentamicin, ampicillin, amoxicillin), recommended consumables (syringes + needles, cotton swabs and CRP (for RCT2)), transport, food and wage loss. All other non-recommended treatments for which households incur expenditure as part of the PSBI treatment will be reported as an additional burden.For each treatment arm, total transport expenses will be added for all days (maximum seven) that transport is used by any caretaker for round-trip travel, and this is then divided by the number of sampled households after conducting the quality checks and removing outliers.For food charges, a similar method of estimation will be used as for transport expenses. Total expenses reported by any caretaker during the treatment period will be summed and then divided by the number of households in the sample, after removing outliers.Wage loss will be calculated per family or per SYI for each of the treatment arms.Average wage/day will be calculated even when annual or monthly wages are given. The average wage for each caregiver will be the average of the range.Average wage/day for each caregiver will be multiplied by the number of days lost for a SYI for any treatment. Maximum days lost by any caretaker will be capped at seven days of recommended treatmentSum of the total wage loss for a family for all caretakers combined will be (A) under any treatment arm.Sum of the number of families that report positive or zero wage loss for any of the caretakers will be (B). SYI where family members did not provide consent will be excluded from the denominator for calculations.Total wage loss per SYI or per family under each treatment arm = A / B

All recommended or non-recommended medical and non-medical costs will be calculated per SYI as an additional burden on households.

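### Staff, medicine and consumable costs are weighted to the enrolled cohort's recommended/partial mix, but the household cost added to them is an unadjusted survey mean

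*Protocol article*

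**What the plan says.** **Provider side.** Under Hospital data, the article separates infants who received at least 80% of treatment from those who received less, and combines them: "Costs for enrolled SYI will be weighted by the proportion of participants receiving 80% recommended treatment and those receiving partial treatment". The stated purpose is that no randomised child is missed. Site-wise and combined analysis plan repeats the rule for the two groups: "Overall costs for enrolled infants will be estimated at the site level using the weighted average of those receiving recommended treatment and those receiving partial".

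**Household side.** Estimation of the household costs sets expenses per infant "based on the number of households in the sample after removing outliers". Site-wise and combined analysis plan says that average household costs "will be calculated at the site level using the household survey sample size as the denominator", and then "For pooled analyses, enrolled SYIs will be used as weights across sites". The sampling rule is "Data will be collected from at least 10% of SYIs enrolled under each arm at each site"; no stratification by completion is stated. Strengths and limitations calls the sample purposive, about 10–15% of enrolled infants in the final nine months, and rules out imputation or adjustment.

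**Combination.** Statistical analysis procedures adds household non-medical costs per infant to medical costs per infant to give societal cost. The CEA section uses societal cost for all randomised infants in both arms.

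**Available but unused.** Under Household cost data, "Data will be collected on the type of treatment arm and duration of treatment". Statistical analysis procedures also plans statistics "per SYI receiving recommended or partial treatment for each of the cost variables at the hospital, as well as at the household level".

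**The concern.** Two per-infant figures are added as if they described the same infants. One is standardised to the cohort's completion mix. The other carries whatever mix the interviewed families happen to have. Weighting by enrolled infants across sites corrects the mix of sites, not the mix of full and partial courses within a site and arm.

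The mixes could differ. The survey is small and purposive, and representativeness is assumed only over time and place. Partial treatment arises from treatment failure, changed treatment, readmission, leaving voluntarily or death (Hospital data), and such families may be easier or harder to interview than others. If the gap differs between arms, or household cost levels do, the error does not cancel in the cost difference. It then passes into the societal incremental cost, the ICER, the incremental net benefit and the reported household burden. The intention-to-treat description in the Abstract would not be fully met for the household part.

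**Working it through.** The document states no partial share, household cost or cost difference, so there is no figure of its own to reproduce. The check compares the two estimators algebraically and then illustrates the result.

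**Step 1: the estimators, per arm.**
- p = partial share in the enrolled cohort; s = partial share in the survey.
- H_R, H_P = mean household cost for recommended and partial courses; r = H_P / H_R.
- Household mean as planned: (1 − s)H_R + sH_P.
- Household mean at the cohort mix, as for staff, medicines and consumables: (1 − p)H_R + pH_P.
- Difference, planned minus standardised: (p − s)(H_R − H_P) = (p − s)(1 − r)H_R.

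The difference is zero if s = p or r = 1. It changes sign if partial cases are over-sampled (s > p) or cost the household more (r > 1).

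**Step 2: assumed inputs (none from the document except the day counts).**
- r = 3/7, meaning household cost proportional to days, with the three days that the article uses for partial provider costs in RCT1.
- H_R = 10 USD intervention, 40 USD control.
- p = 5% intervention, 10–20% control; s = 2–5%.

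**Step 3: household cost difference, intervention minus control (USD).**

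Standardised: 10(1 − 0.05 × 4/7) − 40(1 − p_c × 4/7), which is −28.00 at p_c = 10% and −25.71 at p_c = 20%.

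| s intervention / control | As planned | Overstatement at p_c = 10% | Overstatement at p_c = 20% |
|---|---|---|---|
| 2% / 2% | −29.66 | 5.9% | 15.3% |
| 2% / 5% | −28.97 | 3.5% | 12.7% |
| 5% / 5% | −29.14 | 4.1% | 13.3% |
| 5% / 2% | −29.83 | 6.5% | 16.0% |

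The range is about 3.5% to 16%. In money it is 28.97 − 28.00 = 0.97 USD to 29.83 − 25.71 = about 4.1 USD per infant.

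**Step 4: other assumptions.**
- Equal p of 10% in both arms, s = 2%: −29.66 against −28.29, overstated by 4.8%.
- More partial courses in the intervention arm (p = 15% / 5%), s = 2%: −29.66 against −29.71, or −0.2%.
- Only half of household cost varies with days (r = 5/7), same corners as Step 3: from −29.49 against −29.00 (1.7%) to −29.91 against −27.86 (7.4%).
- r = 1: zero throughout.
- r = 1.25, p = 5% / 20%, s = 2%: −30.15 against −31.88, so the saving is understated by 5.4%.
- Over-sampling, one arm, r = 3/7, p = 20%, s = 40%: the household mean is 12.9% too low (77.14 against 88.57 on a base of 100).
- RCT2 after randomisation, r = 2/5 (two of five days), one arm, no partial cases surveyed: the household mean is 3.1%, 6.4% and 13.6% too high at p = 5%, 10% and 20%.

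**Step 5: limit.** These percentages concern the household saving only. The document gives no provider cost difference, so they cannot be turned into percentages of the societal incremental cost or net benefit.

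**The case against.** Much of the risk is disclosed. Strengths and limitations says that the household sample is purposive, may carry selection bias and will not be adjusted, and it limits its full-cohort claim to provider cost and outcomes. That stands as disclosure. But it is generic, it does not say that one part of the sum is standardised and the other is not, and the Abstract and CEA section still present societal cost as covering all randomised infants.

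It can also be argued that the weighted-average sentence in Site-wise and combined analysis plan is not expressly limited to provider cost, and that a condensed article may leave post-stratification to a fuller plan. Yet that sentence sits among the hospital costs, and household costs have their own paragraph with their own denominator. This is a stated rule, not a gap.

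Two stronger readings are tempting, and the objections to them stand.
- **That the plan inflates the intervention's household saving.** This needs partial families to be under-interviewed and to spend less. Assessors visit all enrolled infants, and interviews may follow up to two weeks after the last assessment, so under-interviewing is only an inference. The three-day figure is a convention for medical cost. Household transport, food and wage loss are counted over up to seven days, and a family whose infant fails treatment or is readmitted may spend as much or more.
- **That all provider cost is standardised to completion.** The shares are explicit for staff, medicines and consumables. Bed costs use length of stay and ward enrolment, and operational costs use infants assessed.

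**Conclusion.** The mismatch in weighting holds on the text: cohort-weighted staff, medicine and consumable costs are added to an unadjusted survey mean, and the sum is presented as societal cost for all randomised infants. The error per arm is (p − s)(H_R − H_P), and its sign and size cannot be determined from the document. The figure of about 3.5% to 16% of the household saving is an illustration that rests on household cost proportional to days, more partial courses in the control arm, and a survey that under-represents them there. Weaken any of these and it shrinks, vanishes or reverses. No size can be given for the societal incremental cost, ICER or net benefit. The point is worth correcting because the mismatch is built into the stated rule and the correction is cheap, not because a material bias has been shown.

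**What to change.** 1. For each arm, tabulate the survey's recommended/partial mix against the enrolled cohort's, using the treatment duration recorded in the household survey.
2. For each arm and site, weight the household means for recommended and partial treatment by the same cohort shares that are used for staff, medicine and consumable costs.
3. Where a site has too few partial-treatment households, apply that arm's partial-to-recommended household cost ratio, pooled over sites.
4. Report the raw survey mean alongside the reweighted one, for the household burden and for the societal results.
5. State that reweighting does not recover deaths or departures that are missing within the partial group, so selection within that group remains.

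The cost is one reweighting step and no new data. The downside is some added variance from small partial-treatment cells, and the assumption that the pooled ratio applies at every site where it is used.
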